### Study Population and Recruitment

This trial will begin to recruit patients with infertility. Once the need for IVF/ICSI was determined and inclusion and exclusion criteria were met, patients were given detailed written information about the trial protocol. Approximately one week later, patients will be approached by the investigator and written informed consent will be obtained at the infertility clinic visit. Baseline blood tests will be performed and basic demographic information including infertility aetiology will be recorded. The patients were then randomly assigned to one of the study groups by the investigators and received the trial regimen.

### Interventions

#### Ovarian Stimulation Protocol

Standard COH protocol with gonadotrophins will be performed using a GnRH-ant protocol. Furthermore, a fixed dosage of GnRH-ant (0.25mg, Cetrorelix; Merck Serono, Darmstadt, Germany) will be used together with 112.5-225 IU/day of recombinant FSH (600IU, Puregon, Merck Sharp & Dohme B.V., Haarlem, Netherlands). Patients will initiate ovarian stimulation treatment with Gn starting on day 3 of the menstrual cycle, the starting dose of Gn will be based primarily on age and BMI, and determined by the patient’s attending physician prior to participation in the study. Subjects will undergo serial transvaginal ultrasound follicle measurements and monitoring of serum oestradiol (E_2_), progesterone (P_4_), and LH levels during the IVF/ICSI cycle to dynamically measured to evaluate the response of ovary, the dose of Gn will be adjusted according to the subject’s response. GnRH-ant (0.25mg/d) will be added on day 5 of ovarian stimulation sustained to the trigger. Trigger when two follicles were ≥ 18mm in diameter or when three follicles were ≥ 17mm in diameter. The following trigger patterns will be used in two groups: (1) hCG-only trigger: injection of recombinant hCG (6500 IU, Ovidrel, European Serono, France) 36 hours before OPU; (2) Dual trigger: co-administration of GnRH-a (Diphereline, 0.1mg, France, Epson) and hCG, 40 and 34 hours prior to OPU, respectively. If a patient has high-risk OHSS (more than 20 follicles over 10 mm in diameter) on the triggering day, a freeze-all strategy will be used. Oocyte retrieval will be performed by transvaginal puncture under transvaginal ultrasound guidance.

#### Embryo Culture

Oocytes will be enzymatically removed of cumulus cells and mature oocytes subjected to *in vitro* fertilization. Zoosperm will be cultured in pre-equilibrated embryo Petri dishes covered with mineral oil in an environment of 5.0% O_2_ and 5.6% CO_2_. The choice of embryos for vitrification will be expected to focus on the inclusion of no less than six blastomeres with ≤ 20% fragmentation. Embryos that presented a fragmentation rate between 20% and 50% will be transferred or vitrified only when they reach the 8-cell stage on Day 3. Day 5 blastocysts with a Gardner score of 3BB or higher were considered to be good quality and suitable for transfer or vitrification (25).

#### Luteal Phase Support Protocols

The decision on fresh or frozen embryo transfer will be made based on the patient’s membranes, serum P_4_ level, embryo score and personal requirements. Routine luteal phase support will be given after embryo transfer (ET), using intramuscular progesterone injection 40mg/day plus progesterone vaginal sustained release gel 90mg/day, discontinued from the day of ET until 10 weeks of gestation.

### Randomization and Blinding

On the trigger day, randomization will begin. Individuals will be assigned to one of two groups, A or B, in a 1:1 ratio by computer, using a random sequence of codes in the order of enrolment. The randomization scheme was entered into an online central randomization database (www.medresman.org). A dedicated data specialist will run the online randomization procedure, who will not be involved in patient recruiting or clinical care. The doctors will be notified of the allocation results *via* email after randomization. Allocation concealment will be guaranteed since the service will not divulge the allocation until after the randomization process, i.e. after the baseline visit. Due to the nature of the intervention, we will not blind the patients and doctors on the assigned groups. However, the trial outcome assessors will be blinded to the intervention.

### Blood Sample Collection

Blood sampling will be performed on the first day of the COH, during the ovarian stimulation, trigger day, oocyte retrieval day, 3 or 5 days after OPU and 14 days after fresh or frozen embryo transfer. Measurement of LH and FSH by time-resolved immunofluorescence. E_2_, P_4_ and hCG will be measured using commercial radioimmunoassay kits for serum measurement according to the manufacturer’s instructions. Freeze serum at -80 °C for use in research situations such as missing samples or analytical errors. If samples are not used, they will be destroyed within 5 years.

### Data Management, Informed Consent and Confidentiality

Data will be recorded electronically. An electronic copy will be stored in an encrypted file on the password protected computer. All data will be stored for 15 years. After that, electronic data will be formatted for removal. The organic samples will be stored in a safely locked temperature-controlled freezer in the centre that can only be used by authorized personnel until the end of the analysis. The sample and participant records do not contain any directly identifiable information. Additional biospecimens will not be retained for ancillary studies.

### Reproductive Outcomes

The primary outcome is MII oocytes rate (percentage of the number of mature oocytes to the number of oocytes retrieved).

The secondary outcomes are number of oocytes retrieved, fertilization rate (the proportion of oocytes that become fertilized), top quality embryos (TQE) rate (percentage of the number of TQE to total embryos obtained), blastula formation rate, embryo implantation rate (percentage of the number of gestational sac to the total transferred embryos), clinical pregnancy rate (percentage of participants with clinical pregnancy), miscarriage rate (percentage of participants with loss of a diagnosed clinical pregnancy before 12 weeks gestation), live birth rate (the proportion of a delivery of one or more living infants), cumulative pregnancy/live birth rates (percentage of participants with clinical pregnancy/live birth after one year of follow-up), severe OHSS rate (percentage of participants with OHSS). TQE was defined as seven or more blastomeres on day three, evenly sized blastomeres, and less than 20% fragmentation, whereas low quality embryos were characterized as anything else. On transvaginal ultrasonography, clinical pregnancy was defined as the appearance of a gestational sac and foetal heartbeat.

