**Figure 1 f1:**
[figure not shown]
Flowchart showing the study process.

**Table 1 T1:** Overview of study visits.

	Enrolment Baseline	COH phase	hCG trigger	Dual trigger	Three days after OPU	Embryo transfer	Pregnancy testing	Follow-up 1 year
Information and counselling	X							
Signing of informed consent	X							
Treatment related data collection		X	X	X	X	X	X	X
Randomization			X	X	X	X		
Transvaginal ultrasound scan	X							X
Ovarian morphology UL scan	X	X	X	X	X	X		
Blood sample	X	X	X	X	X	X	X	

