### Sample Size Estimation

This clinical study is a superiority, randomized parallel controlled trial. GnRH-a+hCG (dual trigger) in group A and hCG-only trigger in group B. MII oocytes rate will be the primary outcome measurement. According to previous data of our centre, the estimated rate of MII oocytes in group B was **40%**, and **70%** in group A after using GnRH-a (40h before OPU) + hCG (34h before OPU) dual trigger, with **standard deviations of 40%** for each group. Suppose that α=0.05 (two-sided) and β=0.10 (90% power), the sample size is calculated to be 40 individuals for each group by PASS 15.0 (NCSS, LLC. Kaysville, Utah, USA.). Assuming a dropout rate of 10%, the sample size 45 individuals for each group will be required. Ultimately, a total of 90 individuals will be recruited for this study.

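### One shared one-year horizon truncates cumulative live birth: term births from transfers after about weeks 13 to 18 cannot be counted, although the pregnancies can

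*Protocol article*

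**What the plan says.** Reproductive Outcomes defines the two cumulative rates together: "cumulative pregnancy/live birth rates (percentage of participants with clinical pregnancy/live birth after one year of follow-up". In the same section live birth is an event at delivery: "live birth rate (the proportion of a delivery of one or more living infants". The last column of Table 1 is "Follow-up 1 year", and nothing is scheduled after it.

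The protocol foresees transfers at different times. Luteal Phase Support Protocols states: "The decision on fresh or frozen embryo transfer will be made based on" several factors, among them serum progesterone, the embryo score and what the patient wants. Ovarian Stimulation Protocol adds that for women at high risk of OHSS on the trigger day "a freeze-all strategy will be used". Embryo Culture covers cleavage-stage embryos, some of which "will be transferred or vitrified only when they reach the 8-cell stage on Day 3", and day-5 blastocysts that are "suitable for transfer or vitrification". No limit is given on the number or timing of transfers.

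Randomization and Blinding places randomisation on the trigger day, leaves patients and doctors unblinded, and blinds the outcome assessors.

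The text does not say when the year starts. It also does not extend follow-up to delivery for women pregnant when the year ends, or credit births to transfers made within it.

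**The concern.** A cumulative rate is meant to capture what one stimulation cycle yields over all its transfers, including later frozen ones. Clinical pregnancy is seen within weeks of a transfer, whereas a term birth follows some eight to nine months later. With one calendar limit for both, a transfer in the second half of the year can add to cumulative pregnancy but cannot add a term birth to cumulative live birth. The denominator is participants, so a woman pregnant at one year stays in it without a birth in the numerator.

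Two things are at stake. The two cumulative rates cannot be read together, because part of any gap between them comes from the calendar and not from pregnancy loss. The truncation also need not be equal between arms. Embryo yield, embryo score and progesterone after the trigger all arise after randomisation, and the choice between fresh and frozen transfer is made by people who know the allocation. The Introduction describes a live baby as the ultimate goal of treatment, so this secondary outcome matters to patients.

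**Working it through.** **The plan's own figures.** The document gives no event rate or sample size for cumulative live birth. Its one calculation, under Sample Size Estimation, concerns the MII oocyte rate: 40% against 70%, SD 40%, "α=0.05 (two-sided) and β=0.10 (90% power". The normal approximation gives 38 per group and the t-test 39, close to the stated 40, and 40 / 0.90 = 44.4 rounds up to the stated 45. Nothing below depends on these, except that with 45 women per arm one woman is 1/45 = 2.2 percentage points.

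**Inputs.** Horizon: one year, 365/7 = 52.14 weeks (Reproductive Outcomes, Table 1). Embryo age at transfer: day 3 or day 5 (Embryo Culture). Gestation at term birth: 37 to 41 weeks, which is an assumption.

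**Formulas.** Gestation is counted from two weeks before fertilisation, so:

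- weeks from transfer to birth = gestation at birth − 2 − (embryo age in days / 7)
- last transfer week with a birth inside the year = 52.14 − weeks from transfer to birth

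| Birth at (weeks) | Transfer to birth, day 3 / day 5 (weeks) | Last transfer week, day 3 / day 5 |
|---|---|---|
| 37 | 34.6 / 34.3 | 17.6 / 17.9 |
| 39 | 36.6 / 36.3 | 15.6 / 15.9 |
| 40 | 37.6 / 37.3 | 14.6 / 14.9 |
| 41 | 38.6 / 38.3 | 13.6 / 13.9 |

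Taking the year as 52 weeks lowers each limit by 0.14 week, so the full range is 13.4 to 17.9 weeks. A cruder check with 38 weeks from conception gives 365 − 38 × 7 = 99 days, or 14.1 weeks.

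**Preterm births.** Birth at 34 weeks moves the limit to 20.6 to 20.9 weeks. From about week 18 onward, therefore, a transfer can add a live birth only if delivery is preterm.

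**Window for pregnancy.** Clinical pregnancy requires a gestational sac and heartbeat. Assuming these are seen 4 to 5 weeks after transfer, pregnancies count for transfers up to 52.14 − 5 = 47.1 or 52.14 − 4 = 48.1 weeks. Transfers from about weeks 13 to 18 up to about weeks 47 to 48 thus count for one rate and, at term, not for the other.

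**Start of the year.** If it starts at the first transfer, a term birth from that transfer takes 34.3 to 38.6 weeks and fits; only repeat transfers after the limit are lost. If it starts at randomisation, a fresh transfer still fits: retrieval is at most 40 hours after the trigger and transfer 3 or 5 days later, so it falls in about the first week. A first frozen transfer that is delayed past the limit would then be lost as well.

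**Follow-up needed.** To capture a 40-week birth from a transfer at the end of the year: 52.14 + 37.6 = 89.7 weeks, about 20 to 21 months.

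**The case against.** Several objections deserve weight.

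- Live birth within one year is a legitimate and interpretable quantity, and a live birth rate with no one-year limit is listed separately. This is true, but that second rate is not cumulative and does not say which transfers it covers. The outcome named cumulative is the one meant to include later transfers.
- The article does not say how women pregnant at one year are classified, and a full protocol or SAP might. This stands in part: no sentence labels them failures. But the stated definition, with participants as denominator and no later contact, leaves them without a counted birth.
- The start of the year is open, so 14 weeks is not a fixed date in the trial. This stands; the limit is relative to a start that has to be assumed.
- The loss may be small. The Introduction calls fresh transfer the preferred option, and the freeze-all rule needs more than 20 follicles over 10 mm in women selected for an antral follicle count of 6 to 15. This also stands. Other frozen transfers are allowed, but their number and timing are not given.

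A reader might infer that close to three quarters of births are lost, since (365 − 99) / 365 = 73%. That is a share of calendar time, not of transfers, pregnancies or births, and would measure the loss only if transfers were spread evenly over the year. A reader might also infer a bias against dual trigger, because more embryos could mean more late frozen transfers. The documents do not support a direction: better embryos could equally bring earlier success and fewer late transfers.

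**Conclusion.** The definition should be changed. As written, cumulative live birth is truncated and rests on a different set of transfers from cumulative pregnancy. Under assumed term delivery at 37 to 41 weeks, the last transfer that can yield a counted term birth falls at about week 13 to 18 of the year. Which transfers are affected depends on the undefined start: repeat transfers only if the year begins at first transfer, and also delayed first frozen transfers if it begins at randomisation.

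The truncation could differ by arm, because transfer timing depends on events and unblinded decisions after randomisation. How many women are affected, and which arm would be favoured, cannot be determined from the documents. Each affected woman would move her arm's rate by 2.2 percentage points at 45 per arm. The point concerns one secondary outcome and leaves the primary outcome and its sample size untouched.

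**What to change.** In Reproductive Outcomes, replace the shared phrase with two matched definitions:

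- the clock starts at randomisation;
- cumulative clinical pregnancy is at least one clinical pregnancy from any transfer of trial-cycle embryos made within 12 months;
- cumulative live birth is at least one live birth from those same transfers, with every resulting pregnancy followed to its end, whenever that falls;
- the denominator for both is all randomised women.

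Add to Table 1 a contact at the end of pregnancy for women still pregnant at 12 months. If a live birth rate at exactly one year is also wanted, report it under that name beside the cumulative rate.

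The cost is telephone follow-up of women still pregnant at 12 months, for up to about nine more months, and later reporting of this one secondary result. Treatment, recruitment, sample size and the timing of the primary analysis do not change.

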**Methods and Analysis:**

We propose a study at the Affiliated Hospital of Shandong University of Chinese Medicine. A total of 90 individuals undergoing COH use a fixed GnRH antagonist protocol. They will be assigned randomly into two groups according to the trigger method and timing: recombinant hCG (6500 IU) will be injected only 36 hours before OPU for final oocyte maturation (hCG-only trigger); co-administration of GnRH-a and hCG for final oocyte maturation, 40 and 34 hours prior to OPU, respectively (Dual trigger). The primary outcome is metaphase-II (MII) oocytes rate. Secondary outcomes are number of oocytes retrieved, fertilization rate, top-quality embryos rate, blastula formation rate, embryo implantation rate, clinical pregnancy rate, miscarriage rate, live birth rate, cumulative pregnancy/live birth rates, and ovarian hyperstimulation syndrome (OHSS) rate.

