#### Exclusion Criteria

(1) Age ≥ 40 years; (2) body mass index (BMI) ≥ 30 kg/m^2^; (3) Individuals with severe OHSS during ovarian stimulation; (4) Patients with endocrine disorders (diabetes, hyperprolactinemia, hypothyroidism, congenital adrenal hyperplasia, Cushing’s syndrome or polycystic ovary syndrome); (5) Untreated moderate and severe endometriosis, submucosal myoma, multiple endometrial polyps, pelvic inflammation, uterine malformation, Asherman syndrome and hydrosalpinx; (6) Patients with abnormal immune function and chromosome karyotype of both spouses.

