### Study Case Discontinuation

Subjects in the study who experience serious adverse reactions, special physiological reactions, other unexpected events, or who are not suitable to continue participating in the trial will be terminated from the trial. Urgent measures will be taken during the study if the subject has a serious complication or if the condition worsens.

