### Data Statistical Analysis

All randomized individuals will be included in the analysis of the primary trial end point (intention-to-treat analysis). For analyses of other outcome variables, only subjects randomized to the study protocol will be included (per-protocol analysis). SPSS version 26.0 and R statistical package version 4.0.0 will be used to analyse all the data. The continuous data will be normalized using the two independent samples t-test and presented as mean ± standard deviation (Mean ± SD). If the distribution is not normal, use nonparametric tests, which are expressed as the median (interquartile range) [M (IQR)]. Categorical data will be presented as frequency (percentage) [n (%)] using chi square test and Fisher’s exact test for expected frequencies less than five. P < 0.05 indicates that the difference is statistically significant.

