### Adverse Events and Data Safety and Monitoring

An independent data safety and monitoring committee will be established to monitor the occurrence of adverse events. During the trial, the principal investigator will be followed up by telephone at any time and subjects will provide details if any adverse events arise. Participants will also be interviewed on the day of oocyte retrieval to determine if any adverse events occur serious adverse events will be recorded separately and will be followed up until resolution.

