## Discussion

In IVF/ICSI technology, the use of a pharmaceutical trigger to drive the final maturation of the oocyte is a crucial step. The LH effect produced by natural cycle lasts for 48 hours. As a common pharmaceutical used as trigger, hCG plays a role in promoting the final maturation of oocytes instead of endogenous LH. But the effect of 10, 000 IU hCG is 20 times greater than that of endogenous LH and can last more than 120 hours (1). Although the effects of hCG are long-lasting and can promote the production of corpus luteum in favour of embryo implantation and ongoing pregnancy. But it is precisely because of its strong and sustained action that leads to an increased risk of OHSS during the hCG trigger cycle. GnRH-a trigger has the advantage of driving the production of endogenous LH and FSH. LH and FSH act synergistically to promote oocyte final maturation and ovulation, which seems to be more favourable for oocyte quality. However, due to the effects of GnRH-a last only 24-36 h, leading to subsequent luteal insufficiency, they adversely affect pregnancy outcomes and live birth rates. Thus GnRH-a trigger still has certain limitations in the clinic.

The use of GnRH-a and a standard dose of hCG at 40 and 34 hours prior to oocyte retrieval was previously found to produce an elevated proportion of low mature oocytes compared to previous hCG trigger cycles and to successfully obtain mature oocytes in a patient with EFS. This study is a prospective, randomized, superiority-controlled trial to investigate whether dual trigger could improve reproductive outcomes in people with NOR, with the aim of identifying a more optimal trigger method. If this trigger method does improve IVF/ICSI outcomes, it may become a routine trigger method to boon more infertile couples. The subsequent results of this study, which may provide some data support for our next randomized controlled trial.

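### The OHSS outcome is labelled severe but counts OHSS of any grade, and the analysis and follow-up rules leave it open to undercounting

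*Protocol article*

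**What the plan says.** Under Reproductive Outcomes, the last secondary outcome reads "severe OHSS rate (percentage of participants with OHSS"). No grade or grading scale accompanies it. The Methods and Analysis paragraph of the abstract lists the same outcome as "ovarian hyperstimulation syndrome (OHSS) rate", without severity.

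Three other sections decide which cases reach that count:

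- **Study Case Discontinuation** ends trial participation for certain women, starting with this group: "Subjects in the study who experience serious adverse reactions".
- **Data Statistical Analysis** applies intention to treat to the primary endpoint. For the other outcomes, "only subjects randomized to the study protocol will be included (per-protocol analysis").
- **Adverse Events and Data Safety and Monitoring** names one fixed interview: "Participants will also be interviewed on the day of oocyte retrieval to determine if any adverse events occur". It adds telephone contact at any time, follow-up of serious events to resolution, and an independent safety committee.

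Table 1 ticks an ovarian ultrasound and a blood sample three days after retrieval and at embryo transfer, and data collection up to the one-year follow-up. Blood Sample Collection lists sampling 3 or 5 days after retrieval and 14 days after transfer.

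**The concern.** OHSS is the outcome in the list aimed at the safety of the trigger. The Introduction and the Discussion both make OHSS risk part of the reason for comparing triggers. Two things could spoil the comparison.

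First, the event is not fixed. One analyst could follow the label and count severe cases only; another could follow the bracketed definition and count all cases. Both could claim to have followed the protocol, and the second would publish a severe OHSS rate that includes mild cases.

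Second, the cases that matter most could be lost. A woman with serious OHSS after the trigger can be terminated and then fall outside a per-protocol set. A woman whose symptoms begin after retrieval meets no further fixed adverse-event interview. Patients and doctors are not blinded, so voluntary reporting after retrieval could differ between arms.

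**Working it through.** **1. Label against numerator.**

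| Place | Name given | Who is counted |
|---|---|---|
| Abstract | OHSS rate | not stated |
| Reproductive Outcomes, label | severe OHSS rate | severe cases implied |
| Reproductive Outcomes, definition | – | all participants with OHSS |

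The second and third rows cannot both hold unless every case is severe. This is a contradiction within one line of the article, not detail left to a longer document.

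**2. Can a case leave the count?** The discontinuation rule ends participation but does not say that the event is discarded. The analysis section puts OHSS, as a non-primary outcome, in a set called per-protocol. Nothing states that terminated women stay in that set. Read together, the two rules allow a serious post-trigger case to leave both numerator and denominator; they do not say that it will.

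**3. When are women asked?** Under Interventions, hCG is given 36 hours before retrieval in the hCG-only arm and 34 hours before in the dual arm. The one fixed interview therefore falls 34 to 36 hours after hCG. Later contacts exist, but the article assigns none of them to OHSS and gives no window over which OHSS is counted.

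**4. How sensitive is the comparison?** The plan gives no figure for OHSS, so there is none to reproduce. Its only sample-size figure is for the MII rate (difference 30 points, SD 40 points, two-sided 5%, 90% power):

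- 2 × (0.40 × (1.960 + 1.282) / 0.30)² = 37.4, so 38 per group. The t-based value is 39, and about 40 with a rank-test allowance. The stated 40 is reproduced within two.
- With 10% dropout: 40 / 0.90 = 44.4, so 45 per group and 90 in total, as stated.

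With 45 per arm, for OHSS:

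- One case: 1/45 = 2.2 percentage points.
- Fisher's exact test, two-sided, denominators kept at 45: 6 against 0 gives P = 0.026; 5 against 0 gives P = 0.056. One missed or regraded case can move the result across the 5% line.
- One of six cases deleted with its denominator: 6/45 = 13.3% becomes 5/44 = 11.4%.
- No cases in 45: one-sided exact 95% upper limit 1 − 0.05^(1/45) = 6.4%, valid only if every case would have been found.

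Fisher power at 45 per arm, under assumed OHSS rates because the documents give none:

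| Assumed rates | Power |
|---|---|
| 1% v 3% | 0.1% |
| 2% v 5% | 1% |
| 5% v 10% | 6% |
| 10% v 20% | 18% |

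The trial cannot test OHSS with useful power across this range. The value of the outcome lies in a complete and correctly graded count.

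**The case against.** The case against has several sound parts.

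- **Capture after retrieval.** A reader might infer that OHSS after retrieval is found only if the woman telephones. Table 1, the later blood samples and the follow-up of serious events contradict that. What stands is narrower: only one adverse-event interview is fixed, and no later contact is assigned to OHSS.
- **The exclusion criterion.** A reader might infer that "Individuals with severe OHSS during ovarian stimulation" deletes outcome events. It names no cycle, and by its wording it concerns stimulation. The article also says "On the trigger day, randomization will begin". On that sequence the criterion acts before allocation and before hCG. It narrows the population and does not remove post-trigger cases from an arm.
- **Duration of hCG action.** The Discussion says the effect "can last more than 120 hours", and a reader might divide 36 by 120 hours and conclude that most cases arise after the interview. The figure is for 10,000 IU, whereas the hCG-only arm receives recombinant hCG 6500 IU. It is a duration of hormone action, not a distribution of OHSS onset. The documents give no share of cases missed.
- **Serious events are recorded.** They are recorded separately and followed to resolution, so a terminated woman's event need not vanish from the safety record. That does not put it into the OHSS rate, which is governed by the analysis set.
- **Loose set definition.** The description of the per-protocol set could be read as all randomised women. If that is meant, the label is wrong and the remedy is the same.
- **Condensed article.** A grading scale and visit forms may sit in the full protocol, so their absence alone is no fault. The contradiction between label and definition is printed here and cannot be explained that way.

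**Conclusion.** The point holds as mislabelled and open to undercounting. The mislabelling is certain on the text: any-grade cases would be reported under the name of severe OHSS. The undercounting is a risk. It depends on how the per-protocol set treats terminated women and on whether staff ask about OHSS at later visits. Its extent cannot be calculated from the documents.

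The figures of 2.2 points per case and six against none follow from 45 women per arm. They show how far a single case can move the comparison, not how many cases will be lost. A reader might go further and conclude that the safety comparison will be wrong; the documents do not establish that. The primary outcome is unaffected. The correction is worth making because it concerns a safety outcome and costs little.

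**What to change.** 1. **Reconcile label and numerator.** Replace the single outcome with two, any OHSS and severe (or moderate/severe) OHSS, both graded on one named scale, and use the same names in the abstract.
2. **Change the analysis set for OHSS.** Analyse it in all randomised women who received any trigger, in the arm to which they were randomised. Keep women terminated from the trial in numerator and denominator. This concerns only counting; it leaves the discontinuation rule as it is.
3. **Record OHSS at contacts already scheduled.** Add one checklist line at 3 or 5 days after retrieval, at embryo transfer and 14 days after transfer, asked in the same way in both arms, and state the counting window.

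The cost is revised outcome wording, a sentence on the analysis set and slightly more recording. No new visit is needed. The reported OHSS rate may be higher than under the present rules.
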